### Sample Size Calculation

A cluster sampling method with PPS procedure was assigned. Sample size was calculated in screening group (Masjed-Soleyman) using the following formula (Figure 2) and assumption, resulting in 1537 subjects.

The same steps (except for ε=0.2) were used for calculation of sample size in no screening group (Shushtar), resulting in 900 subjects. Using the cluster sampling method, 1600 and 900 first trimester mothers were selected from among those receiving prenatal care in health centers in urban regions of Masjed-Soleyman and Shushtar, respectively.

Since the prevalence of the specified event is untreated or unrecognized and the number of people who have the risk factor (P) is high in the population, consequently, sample size needed for screening is considered sufficient. In other words, we define a correction coefficient by (1/P) for estimated sample size (n), and then we expect n (1/P) number of people to find the 0.15 difference with 5% significance level.

To compare different regimens used for vitamin D deficiency in the screening group, the sample size in each group was calculated based on the following formula (Figure 3) and assumption:

Considering loss to follow up of 10%, a total number of 100 in each study group was considered adequate.

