## Results

Recruitment commenced in July, 2014 and as estimated, nearly 3.5 years is needed to complete the study. Currently, this study is in the stage of analyzing data.

The baseline characteristics of the study participants are shown in Tables 2 and 3, which indicate no significant difference between the participants of the 2 cities.

**Table 2 table2:** Baseline characteristics of study participants, overall and by study sites.

Characteristics	Masjed-Solayman n=900	Shushtar n=900	Overall n=1800	*P* value^b^
Age (year)	29 (25-32)^a^	29 (25-32)	29 (25-32)	.63
Marriage age (year)	20 (18-22)	19 (17-23)	19 (17-22)	.08
First delivery age (year)	20 (18-22)	20 (18-21)	20 (18-22)	.57
First pregnancy age (year)	21 (19-24)	20 (18-24)	21 (19-24)	.08
Pregnancy week	10 (9-12)	10 (9-12)	9 (10-12)	.07
Gravity	2 (1-3)	2 (1-3)	2 (1-3)	.95
Parity	1 (0-2)	1 (0-2)	1 (0-2)	.86
Number of abortions	0 (0-0)	0 (0-0)	0 (0-0)	.96
Number of children	1 (0-2)	1 (0-2)	1 (0-2)	.79
Vitamin D4 (ng/ml)	11 (7-16)	11 (7-16)	11 (7-16)	.96
SBP (6-10w) (mg/dl)	115 (110-120)	120 (110-120)	120 (110-120)	.87
DPB (6-10w) (mg/dl)	70 (60-70)	70 (70-70)	70 (60-70)	.65
Maternal weight (6-10 w)	65 (59-70)	64 (59-70)	64 (59-70)	.98

^a^Median (interquartile range).

^b^*P* value obtained from independent samples distribution nonparametric Mann-Whitney test (the significance level is <.05).

**Table 3 table3:** Baseline qualitative characteristics of the study participants, overall and by study site.

Participant characteristics		Masjed Solayman		Shushtar		Overall			
		Frequency (n)	Percentage (%)	Frequency (n)	Percentage (%)	Frequency (n)	Percentage (%)	^a^*P* value	

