**Occupation**										
	Worker	14	1.60	21	2.30	35	1.90	.46
	Clerk	135	15.00	119	13.20	254	14.10	
	Self-employed	111	12.30	117	13.00	228	12.70	
	Housewife	640	71.10	643	71.40	1283	71.30	
	Total	900	100.00	900	100.00	1800	100.00	

^a^The chi-square statistic is significant at the .05 level.

^b^Fisher exact test results is significant at the .05 level.

For the second phase of the study, as statistically was calculated, we needed 800 women, therefore the remaining women were referred to a specialist for further treatments. However, in terms of baseline features except for vitamin D levels, there was no significant difference between the initial sample in Masjed-Soleyman and those who were allocated to intervention (Table 4). The difference for vitamin D is ignorable though.

**Table 4 table4:** Comparison of baseline characteristics between the initial sample of Masjed-Soleyman participants and those allocated to intervention.

Baseline variables	Initial sample (n=1581)	Allocated for intervention (n=900)	*P* value^a^
Age (year)	29 (25-32)^b^	29 (25-32)	.77
First pregnancy age (year)	20 (18-22)	20 (18-22)	.94
First delivery age (year)	20 (18-22)	20 (18-22)	.73
Gestational age (week)	10 (9-12)	10 (9-12)	.97
Vitamin D	11.9 (8-17)	11.2 (7-16)	.01
Number of children	^b^1 (0-2)	1 (0-2)	.67
Gravity	2 (1-3)	2 (1-3)	.62
Parity	1 (0-2)	1 (0-2)	.47
Number of abortions	0 (0-0)	0 (0-0)	.94

^a^*P* value obtained from nonparametric Mann-Whitney test for nonnormal variables.

^b^Median (interquartile range, Q1-Q3).

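### Tables 2 and 3 compare the cities using 900 unidentified Masjed-Soleyman women instead of the 1581 in the initial sample, and the claim of no difference between the cities is unsupported

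*Protocol article*

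**What the plan says.** Under Sample Size Calculation, the protocol article states that "1600 and 900 first trimester mothers were selected from among those receiving prenatal care", in Masjed-Soleyman and Shushtar respectively. In the Results, Table 4 has a column for Masjed-Soleyman headed "Initial sample (n=1581" and a second headed "Allocated for intervention (n=900".

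Table 2, captioned as overall and by study site, has columns headed "Masjed-Solayman n=900" and "Shushtar n=900". Every total in Table 3 is also 900 per city. The vitamin D row of Table 2 reads "Vitamin D4 (ng/ml) 11 (7-16) 11 (7-16) 11 (7-16) .96".

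Two conclusions follow in the Results. The first is that Tables 2 and 3 are tables "which indicate no significant difference between the participants of the 2 cities". The second concerns the selected group against the full Masjed-Soleyman sample in Table 4: "The difference for vitamin D is ignorable though".

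**The concern.** A table of baseline characteristics by site should describe the people recruited at each site. Here one column is all of Shushtar and the other is 900 of 1581 women from Masjed-Soleyman, with no statement of how the 900 were chosen. The only Masjed-Soleyman group of that size elsewhere in the article is the selected group in Table 4, whose vitamin D is lower than that of the whole city sample.

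This matters because the screening question is answered by comparing one city with the other. The First Phase section says that one of two similar cities was assigned to intervention and describes no randomisation between them. The case for comparability therefore rests on these tables and on adjustment in the analysis. If the column shown was chosen in a way related to vitamin D, it cannot show that the cities were alike in vitamin D at recruitment.

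**Working it through.** **Inputs**
- Full Masjed-Soleyman sample (Table 4): n=1581, vitamin D 11.9 (8-17) ng/ml.
- Selected group (Table 4): n=900, 11.2 (7-16); P=.01 against the full sample.
- Masjed-Soleyman in Table 2: n=900, 11 (7-16). Shushtar in Table 2: n=900, 11 (7-16). P=.96 between them.
- All P values below are two-sided; the article does not state sidedness.

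**Step 1: reproduce Table 4's P=.01**
- Normal approximation: SD = IQR/1.349 = 9/1.349 = 6.67 ng/ml. The difference is 11.9 − 11.2 = 0.7, so z = 0.7/(6.67 × √(1/1581 + 1/900)) = 0.7/0.279 = 2.51 and P=.012.
- Mann-Whitney statistic from distributions drawn piecewise through the printed quartiles (assumed range 2 to 40 ng/ml): z=2.52, P=.012.

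Both agree with the printed .01.

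**Step 2: full Masjed-Soleyman sample against Shushtar, from the quartiles**

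This step does not need the two groups of 900 to be the same women. Table 2 rounds Shushtar's median to 11, so three values were tried.

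| Shushtar median | Mann-Whitney z | P |
|---|---|---|
| 11.0 | 2.76 | .006 |
| 11.2 | 2.52 | .012 |
| 11.4 | 2.28 | .023 |

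**Step 3: the same contrast from the printed P values**

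This step assumes that the two groups of 900 have the same vitamin D distribution.
- The standard error of the Mann-Whitney probability is √((n1+n2+1)/(12·n1·n2)).
- For 1581 v 900 it is √(2482/17,074,800) = 0.01206. P=.01 means z=2.576, a shift of 0.0311 from one half.
- For 900 v 900 it is √(1801/9,720,000) = 0.01361. P=.96 means z of about 0.05, a shift of 0.0007 in either direction.
- Combined: z = (0.0311 ± 0.0007)/0.01206, giving P of .008 to .012. If the printed .01 stands for anything from .005 to .0149, the range is .004 to .017.

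**Step 4: size**

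The difference is 0.7 ng/ml (Shushtar median 11.2) to 0.9 ng/ml (11.0). Divided by 6.67, that is 0.10 to 0.13 SD.

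**Step 5: sensitivity to rounding**
- Rounding the quartiles as favourably as possible to the claim of no difference gives P=.33. Those values would also give .33 for Table 4, where .01 is printed, so they do not fit the article.
- Simulating from lognormal fits gives P<.05 in 88% of runs with a Shushtar median of exactly 11.0, about 68% to 73% with 11.2, and about 39% to 44% with 11.4.

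**Step 6: are the 900 selected?**

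If Table 4's 900 lie within the 1581, its test compares overlapping groups. The implied gap between the 900 and the 681 left out is 0.7 × 1581/681 = 1.6 ng/ml, with z of about 4.9. Membership of that group was then related to vitamin D.

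**Step 7: Table 3 on its own figures**

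Pearson chi-square tests reproduce all 11 printed P values (those printed as .001 come out smaller). Six are below .05:
- spouse education .010
- accommodation .004
- sun exposure <.001
- cream <.001
- gloves .002
- veil <.001

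Some of the differences are large. Chador is worn by 328/900 (36.4%) against 502/900 (55.8%), and the highest sun-exposure category holds 37/900 (4.1%) against 119/900 (13.2%).

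**The case against.** The strongest reply is that nothing is concealed and little is at stake. Table 4 prints both vitamin D summaries and P=.01, and the text mentions the difference. A gap of 0.1 SD reaches significance mainly because about 2,500 women are compared, and a baseline P value does not measure confounding. This stands as to size. It does not rescue a sentence that denies any significant difference.

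The 900 may also be the relevant group. Deficient women who were not allocated were referred to specialists, and Overall Study Design speaks of Masjed-Soleyman women with deficiency entering the screening contrast. The 900 could be 800 treated women plus 100 with normal status. That is a conjecture: the article does not say so, and The Second Phase describes the contrast as the city's participants against Shushtar's. The reply shows that a separate column for a followed subset may be needed. It does not show that an unlabelled subset can stand for the city.

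Four stronger readings are tempting, and the documents do not carry them:
- **That the cities certainly differ in vitamin D.** No test of 1581 against Shushtar is printed, and Step 5 shows how far the result depends on rounding.
- **That the two groups of 900 are the same women.** This is likely, since most shared rows agree, but it is not stated, and first pregnancy age is 21 (19-24) in Table 2 and 20 (18-22) in Table 4.
- **That the screening comparison will be confounded.** Statistical Analysis already plans generalized linear models with covariates; it does not name them.
- **That the prevalence estimate will be biased.** No passage takes prevalence from the 900 or from the pooled 1800; the first phase is built on 1600 and 900.

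**Conclusion.** The point holds as a fault in the baseline comparison and in the conclusion drawn from it. Tables 2 and 3 show an unidentified 900 of 1581 Masjed-Soleyman women, with the vitamin D profile of a selected group. On the full sample, Shushtar's baseline vitamin D is lower by about 0.7 to 0.9 ng/ml, about 0.1 SD, with a derived P near .01 in place of the printed .96. That P value rests on rounded quartiles and an assumed distribution shape, or on treating the two groups of 900 as having the same vitamin D distribution.

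The second ground needs no derivation: six of 11 printed P values in Table 3 contradict the sentence, and four of the six variables (sun exposure, cream, gloves and veil) concern exposure of the skin to sunlight. The statement of comparability should be corrected. The vitamin D gap is small and does not by itself undermine the screening comparison.

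**What to change.** - Show Tables 2 and 3 for all 1581 Masjed-Soleyman women against the 900 in Shushtar. If the followed screening arm is a subset, add it as a separate column and say how it was formed.
- Withdraw the sentence claiming no significant difference between the cities and the one dismissing the vitamin D difference in Table 4. Report the differences and their size.
- In the generalized linear model already planned for screening versus no screening, name baseline 25(OH)D and the six Table 3 characteristics above as covariates. Baseline 25(OH)D is available in both cities, since the stored Shushtar samples are assayed at the end of the study.
- Report prevalence by city from the full recruited samples.

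The cost is re-running two descriptive tables and adding measured covariates to an existing model. The comparability statement becomes less favourable.

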**Education**										
	Illiterate	37	4.10	17	1.90	54	3.00	.07
	Primary	132	14.70	135	15.00	267	14.80	
	Guidance school	218	24.20	240	26.70	458	25.40	
	High school	319	35.40	313	34.80	632	35.10	
	Academic	194	21.60	195	21.70	389	21.60		
	Total	900	100.00	900	100.00	1800	100.00	
**Spouse education**									
	Illiterate	33	3.70	24	2.70	57	3.20	.01^a^
	Primary	136	15.10	144	16.00	280	15.60	
	Guidance school	178	19.80	207	23.00	385	21.40	
	High school	249	27.70	190	21.10	439	24.40	
	Academic	304	33.80	335	37.20	639	35.50	
	Total	900	100.00	900	100.00	1800	100.00	
**Spouse occupation**									
	Worker	377	41.90	332	36.90	709	39.40	.08
	Clerk	205	22.80	213	23.70	418	23.20	
	Self-employed	318	35.30	355	39.40	673	37.40	
	Total	900	100.00	900	100.00	1800	100.00	
**Accommodation**									
	Apartment	431	47.90	371	41.20	802	44.60	.004^a^
	House	469	52.10	529	58.80	998	55.40	
	Total	900	100.00	900	100.00	1800	100.00	
**Sun exposure**										
	<5	319	35.40	264	29.30	583	32.40	.001^a^
	May-15	383	42.60	282	31.30	665	36.90	
	15-30	161	17.90	235	26.10	396	22.00	
	>30	37	4.10	119	13.20	156	8.70	
	Total	900	100.00	900	100.00	1800	100.00	
**Cream**									
	Mostly	310	34.40	174	19.30	484	26.90	.001^a^
	Sometimes	321	35.60	386	42.90	707	39.20	
	Always	269	29.90	340	37.80	609	33.80	
	Total	900	100.00	900	100.00	1800	100.00	

**Sun glass**									
	Yes	326	36.20	297	33.00	623	34.60	.15
	No	574	63.80	603	67.00	1177	65.40	
	Total	900	100.00	900	100.00	1800	100.00	
**Gloves**									
	Yes	193	21.40	143	15.90	336	18.70	.002^a^
	No	707	78.60	757	84.10	1464	81.30
	Total	900	100.00	900	100.00	1800	100.00	

**Veil**									
	Chador	328	36.40	502	55.80	830	46.10	.001^a^
	Uniform	572	63.60	398	44.20	970	53.90	
	Total	900	100.00	900	100.00	1800	100.00		
**Spouse smoke**									
	Yes	181	20.10	163	18.10	344	19.10	.28
	No	719	79.90	737	81.90	1456	80.90	
	Total	900	100	900	100.00	1800	100.00	
**Occupation**										
	Worker	14	1.60	21	2.30	35	1.90	.46
	Clerk	135	15.00	119	13.20	254	14.10	
	Self-employed	111	12.30	117	13.00	228	12.70	
	Housewife	640	71.10	643	71.40	1283	71.30	
	Total	900	100.00	900	100.00	1800	100.00	

^a^The chi-square statistic is significant at the .05 level.

^b^Fisher exact test results is significant at the .05 level.

For the second phase of the study, as statistically was calculated, we needed 800 women, therefore the remaining women were referred to a specialist for further treatments. However, in terms of baseline features except for vitamin D levels, there was no significant difference between the initial sample in Masjed-Soleyman and those who were allocated to intervention (Table 4). The difference for vitamin D is ignorable though.

**Table 4 table4:** Comparison of baseline characteristics between the initial sample of Masjed-Soleyman participants and those allocated to intervention.

Baseline variables	Initial sample (n=1581)	Allocated for intervention (n=900)	*P* value^a^
Age (year)	29 (25-32)^b^	29 (25-32)	.77
First pregnancy age (year)	20 (18-22)	20 (18-22)	.94
First delivery age (year)	20 (18-22)	20 (18-22)	.73
Gestational age (week)	10 (9-12)	10 (9-12)	.97
Vitamin D	11.9 (8-17)	11.2 (7-16)	.01
Number of children	^b^1 (0-2)	1 (0-2)	.67
Gravity	2 (1-3)	2 (1-3)	.62
Parity	1 (0-2)	1 (0-2)	.47
Number of abortions	0 (0-0)	0 (0-0)	.94

^a^*P* value obtained from nonparametric Mann-Whitney test for nonnormal variables.

^b^Median (interquartile range, Q1-Q3).

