**Methods:**

This was a two-phase study. First, a population-based cross-sectional study was conducted; recruiting 1600 and 900 first trimester pregnant women from health centers of Masjed-Soleyman and Shushtar, respectively, using stratified multistage cluster sampling with probability proportional to size (PPS) method. Second, to assess the effect of screening strategy on maternal and neonatal outcomes, Masjed-Soleyman participants were assigned to a screening program versus Shushtar participants who became the nonscreening arm. Within the framework of the screening regimen, an 8-arm blind randomized clinical trial was undertaken to compare the effects of various treatment protocols. A total of 800 pregnant women with vitamin D deficiency were selected using simple random sampling from the 1600 individuals of Masjed-Soleyman as interventional groups. Serum concentrations of 25(OH)D were classified as: (1) severe deficient (<10ng/ml), (2) moderate deficient (10-20ng/ml), and (3) normal status (>20ng/ml). Those with severe and moderate deficiency were randomly divided into 4 subgroups and received vitamin D3 based on protocol and were followed until delivery. Data was analyzed according to the intention-to-treat principle.

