## Methods

### Overall Study Design

This was a 2-phase population-based study. The first phase comprised a population-based cross-sectional study in which 1600 and 900 first trimester pregnant women attending health centers of Masjed-Soleyman and Shushtar, Khuzestan province, Iran were recruited using stratified multistage cluster sampling with probability proportional to size (PPS) method [33]. In the second phase of this study, within the framework of screening regimen, Masjed-Soleyman participants with vitamin D deficiency were assigned to a screening program versus Shushtar participants (as nonscreening arm) to assess the effectiveness of various treatment regimens. Pregnancy outcomes including preterm delivery, miscarriage, preeclampsia, gestational diabetes, and type of delivery and neonatal outcomes including birth weight (gr), head circumference (cm), height (cm), APGAR score 1, 5 minute, icterus, cord falling off time (day), serum calcium (mg/dl) level, and cord concentration of 25(OH)D (ng/ml) were recorded.

Shushtar participants (as nonscreening arm) served as controls and were followed till delivery and any adverse pregnancy outcomes were assessed.

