### The Second Phase

In the second phase of the study, to assess the effect of screening strategy on maternal and neonatal outcomes, Masjed-Soleyman participants were assigned to a screening program versus Shushtar participants acting as the nonscreening arm. Within the framework of the screening regimen, an 8-arm blind randomized clinical trial was undertaken to compare the effects of various treatment protocols. Due to the cost and complexity of the process, 800 pregnant women with vitamin D deficiency from Masjed-Soleyman were randomly allocated to 1 of the designed intervention programs according to the study Figure 1. The remaining women with vitamin D deficiency were referred to specialists for further treatments. Participants of Shushtar did not receive any vitamin D supplementation. However, the comparison of the basic confounders between the initial recruited sample in Masjed-Solayman and the women allocated to intervention indicated no statistically significant difference and hence no selection bias occurred during the allocation of treatment (Table 4).

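### Table 4 compares the allocated women with a sample that already contains them, using a test for independent groups, so its P values are too large and the no-selection-bias statement does not follow

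*Protocol article*

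**What the plan says.** - **Recruitment.** Overall Study Design gives "1600 and 900 first trimester pregnant women attending health centers of Masjed-Soleyman and Shushtar" as the phase-one sample.
- **Source of the treated women.** The Abstract says 800 deficient women were "selected using simple random sampling from the 1600 individuals of Masjed-Soleyman". The Second Phase section also gives 800 as the number allocated, and the Results text says 800 were needed. The remaining deficient women were referred to specialists.
- **Table 4 (Results).** The title is "Comparison of baseline characteristics between the initial sample of Masjed-Soleyman participants and those allocated to intervention". The columns are the initial sample, n=1581, and those allocated, n=900. The footnote names the Mann-Whitney test. Vitamin D is 11.9 (8-17) against 11.2 (7-16), P=.01. The other eight P values run from .47 to .97.
- **Conclusion in Methods, The Second Phase.** The comparison "indicated no statistically significant difference and hence no selection bias occurred during the allocation of treatment".
- **Conclusion in Results.** The text before Table 4 makes an exception for vitamin D and adds: "The difference for vitamin D is ignorable though".
- **Eligibility.** Blood Assessments puts Masjed-Soleyman women above 20 ng/ml among the controls. Only women with severe or moderate deficiency could be allocated to a regimen.

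**The concern.** Whether selection occurred is a question about those taken against those not taken. Table 4 instead sets those taken against everyone, themselves included, and uses a test whose null distribution assumes two independent groups. Sharing most of the women pulls the two columns together, and the test does not allow for this. Large P values are then partly a product of the layout, and even a valid non-significant test would not show that selection was absent.

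The reference column also mixes in women who were ineligible for treatment. A vitamin D difference is expected from that rule alone, so the table cannot show whether the deficient women who were treated resemble the deficient women who were not.

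At stake is how well the treated group represents the deficient women found by screening. That matters for reading the regimen results more widely and for knowing who the treated women are when the screening city is compared with the non-screening city.

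**Working it through.** **Inputs.** N=1581, m=900 and the P values come from Table 4; 1600 recruits from Overall Study Design; 800 allocated from the Abstract, The Second Phase and the Results text. A two-sided 5% level is assumed.

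**1. Overlap.** 1581 + 900 = 2481. With at most 1600 distinct women, at least 2481 − 1600 = 881 are in both columns. Since the allocated women were drawn from the sample, full nesting (900) is the natural reading.

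**2. Is the printed P consistent with a test that ignores overlap?** An exact check needs individual data. With lognormal shapes matched to the printed medians and quartiles (an assumption), and 1581 and 900 treated as independent, the Mann-Whitney test gives P of about .013 to .016. That is close to the printed .01.

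**3. Null spread of the test statistic.** In units of the outcome variance:
- Variance the test assumes: 1/N + 1/m = 1/1581 + 1/900 = 0.001744
- True variance with k shared women: 1/N + 1/m − 2k/(N·m)
- With k = 900: 0.001744 − 2/1581 = 0.000479
- Ratio of standard deviations: √(0.000479/0.001744) = 0.524

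The exact rank variances agree: √[(N−m)·m·(N+1) / (N·m·(N+m+1))] = √(681 × 1582 / (1581 × 2482)) = 0.524. A simulation of 400,000 runs also gave 0.524.

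**4. True size of the nominal 5% test**, 2·[1 − Φ(1.96/ratio)]:

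| Case | Ratio | True size |
|---|---|---|
| 900 nested in 1581 | 0.524 | 0.0002 |
| Only 881 shared | 0.538 | 0.0003 |
| 800 nested in 1581 | 0.573 | 0.0006 |

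**5. Power**, overlapping test against a test of 900 versus the other 1581 − 900 = 681, for a true difference between those two groups:

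| Difference (SD) | Overlapping | Disjoint |
|---|---|---|
| 0.10 | 4% | 50% |
| 0.142 | 17% | 80% |
| 0.20 | 58% | 98% |
| 0.25 | 88% | 99.8% |

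**6. The eight non-significant rows after allowing for overlap** (printed z divided by 0.524; ties in the counts ignored): age .77 → .58; first pregnancy age .94 → .89; first delivery age .73 → .51; gestational age .97 → .94; children .67 → .42; gravidity .62 → .34; parity .47 → .17; abortions .94 → .89. None crosses .05.

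**7. What eligibility alone would do to vitamin D.** Fit a lognormal to the initial sample: log-scale SD = ln(17/8)/(2 × 0.6745) = 0.559, median 11.9. About 82% then lie at or below 20 ng/ml, and their median is near 10.5. Restriction to deficient women therefore predicts a gap of about 11.9 − 10.5 = 1.4 ng/ml. The printed gap is 11.9 − 11.2 = 0.7.

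**8. The two statements side by side.** Methods reports no significant difference. Table 4 prints P=.01 for vitamin D against a .05 threshold, and the Results text makes an exception for it. Both cannot stand. This point needs no recalculation.

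**The case against.** The best case for the authors has four parts.

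- **The table is descriptive.** No planned endpoint analysis uses it, and in the eight other rows the printed medians and quartiles are identical in the two columns. That similarity does not depend on the P values. This stands, and it limits the size of the problem.
- **Selection was by simple random sampling**, according to the Abstract, which protects by design. This stands as an argument, but it is not the one the Methods sentence gives: that sentence infers no bias from the test.
- **The test is not powerless.** A reader might infer from a size of 0.0002 that it almost cannot reject. That goes too far: it has 88% power at 0.25 SD and did reject for vitamin D.
- **The vitamin D gap may be harmless.** A reader might divide the printed z by 0.524 (2.576/0.524 = 4.92, P about 1e-6), or scale the 0.7 gap by 1581/681 to 1.6 ng/ml, and present these as corrected values showing strong selection. The documents do not support that. The 681 remaining women include those above 20 ng/ml, so these figures mix in the eligibility rule. Step 7 shows that eligibility could account for the whole gap, and among deficient women the difference may shrink or vanish.

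The count of 900 is itself uncertain, since the text says 800. Table 2 also shows 900 Masjed-Soleyman women with vitamin D 11 (7-16), so the Table 4 column may not be the allocated women alone. That is an inference, but it must be settled before any row is interpreted.

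**Conclusion.** The concern holds in a limited form. The Table 4 columns overlap by at least 881 women, the Mann-Whitney test does not apply to them as run, and its P values are too large (true size about 0.0002 with 900 nested, 0.0006 with 800). With ineligible women in the reference column, the table cannot answer the selection question. The Methods conclusion does not follow and contradicts the vitamin D row.

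The documents do not show that selection bias occurred, only that this table cannot exclude it. They give no reason to doubt the randomised comparisons between regimens, because selection into the trial does not bias contrasts among women randomised within it. The issue is representativeness and who is in the treated group.

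The sizes assume two-sided testing and that the allocated women are a subset of the 1581. Step 7 also assumes a lognormal shape. The adjusted P values in step 6 still use a remainder that includes ineligible women, so they show what overlap does and do not replace the comparison among deficient women.

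**What to change.** 1. Reconcile n=900 in Table 4 with the 800 women stated as allocated in the Abstract, The Second Phase and the Results text, and say who forms the column.
2. Rebuild Table 4 on disjoint groups: deficient women allocated against deficient women not allocated (referred), separately within the severe and moderate classes. Report standardised differences with 95% confidence intervals. Show women above 20 ng/ml in a separate column.
3. In The Second Phase, withdraw the inference of no selection bias. In Results, withdraw the description of the vitamin D difference as negligible. Put the estimated differences in both places so that the two sections agree.
4. If vitamin D still differs within class, say that the regimen results describe the allocated women.

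The cost is one table re-run on data already collected and a few reworded sentences. The intervals will be wider than the present table suggests, because the comparison group will be smaller than 1581. The vitamin D difference could come out larger or smaller than 0.7 ng/ml.

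### Table 4 labels 900 women as allocated where the text randomises 800 deficient women, and as printed it cannot support the statement that allocation was free of selection bias

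*Protocol article*

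**What the plan says.** Three places in the protocol article give the same count.

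- Abstract, Methods: "A total of 800 pregnant women with vitamin D deficiency were selected using simple random sampling".
- The Second Phase: "800 pregnant women with vitamin D deficiency from Masjed-Soleyman were randomly allocated to 1 of the designed intervention programs".
- Results, directly above Table 4: "we needed 800 women, therefore the remaining women were referred to a specialist for further treatments".

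The design agrees with them. The Second Phase says "an 8-arm blind randomized clinical trial was undertaken", and Sample Size Calculation says "a total number of 100 in each study group was considered adequate", with 10% loss to follow-up already allowed for. Randomization and Blinding splits each severity class (below 10, and 10-20 ng/ml) into four subgroups. Women above 20 ng/ml are controls (Blood Assessments; Women With Normal Status).

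Table 4 compares a column headed "Initial sample (n=1581" with one headed "Allocated for intervention (n=900" by the Mann-Whitney test. Vitamin D is 11.9 (8-17) in the first and 11.2 (7-16) in the second, P=.01.

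The Second Phase cites Table 4 for the absence of any significant difference in baseline confounders, and infers that allocation introduced no selection bias. The Results text beside the table does except vitamin D, but calls its difference negligible.

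**The concern.** The count in Table 4 contradicts the text around it. The vitamin D row suggests that this is more than a mistyped n, because the values do not look like those of a group made up only of deficient women.

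This matters because the table carries an argument. It is the only evidence offered that the women taken into the trial were fairly drawn from the deficient women found at screening. If the column is not the randomised set, if the test does not suit overlapping groups, and if the citing sentence misreports the one significant row, then that evidence falls away. What is at stake is the account of how the randomised women were selected, and so to whom the results apply. The randomised comparison between arms is not at stake.

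**Working it through.** **1. The count.** 8 arms × 100 = 800, which reproduces the text. Table 4 has 900, and (900 − 800)/800 = 12.5%. Loss to follow-up does not explain the excess, since the 100 per arm already includes it.

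**2. Vitamin D in the column.** Inputs: the initial-sample quartiles 8, 11.9 and 17 (Table 4) and the cut-offs 10 and 20 ng/ml. Lognormal, gamma and Weibull curves F were fitted to those quartiles, cut at 10 and 20, and re-weighted to s severe, m moderate and n normal women. The p-quantile of the mixture is the x that solves

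[s·min(F(x), F(10))/F(10) + m·max(0, min(F(x), F(20)) − F(10))/(F(20) − F(10)) + n·max(0, F(x) − F(20))/(1 − F(20))]/(s + m + n) = p.

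Results (range over the three curves, ng/ml):

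| Group | Q1 | Median | Q3 |
|---|---|---|---|
| 400 severe + 400 moderate | 6.8-7.3 | 10.0 | 13.7-14.1 |
| Random draw of deficient women | 7.3-7.5 | 10.4-11.0 | 14.0-14.7 |
| 400 severe + 500 moderate | 7.2-7.6 | 10.7-10.8 | 14.1-14.6 |
| 400 + 400 + 100 above 20 | 7.2-7.6 | 10.8-11.0 | 15.5-16.0 |
| **Table 4, n=900** | **7** | **11.2** | **16** |

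With equal numbers below and above 10 ng/ml, the median sits at the boundary whatever the curve. The deficient-only mixes all miss the upper quartile by more than 1 ng/ml. Only the mix with some women above 20 comes close to all three quartiles. Table 2 has a Masjed-Soleyman group of 900 with vitamin D 11 (7-16), which looks like the same women.

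**3. The test.** Assume that the 900 are all among the 1581, as the table title implies. The remainder is 1581 − 900 = 681. For a subset of size a within a whole of size N, the disjoint comparison has z larger than the subset-versus-whole z by √((N + a)/(N − a)):

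√((1581 + 900)/681) = √(2481/681) = 1.91.

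The printed test thus needs a disjoint-group z of 1.96 × 1.91 = 3.74 before it reaches P=.05. For the vitamin D row, P=.01 is z = 2.58, and 2.58 × 1.91 = 4.9. Treating medians as if they were means, the 0.7 ng/ml gap becomes 0.7 × 1581/681 = 1.6 ng/ml against the other 681.

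**4. What gap the design produces by itself.** Take a lognormal with μ = ln 11.9 and σ = (ln 17 − ln 8)/(2 × 0.6745) = 0.559. The 1581 women then split into about 597 severe, 705 moderate and 279 normal. Removing 400, 400 and 100 leaves about 197, 305 and 179 (681 in all). The median of that remainder is about 13.5, against 10.8 in the 900. That is a gap of about 2.6 ng/ml, with perfectly random sampling within each severity class.

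**The case against.** **Figure 1.** The article sends the reader there for the allocation scheme, and it was not available for this check. It may explain the 900, for instance as eight arms of 100 plus a comparison group of 100. This stands: who the extra women are cannot be settled here. It does not remove the contradiction, because a column that includes controls is mislabelled, and if all 900 were allocated then 800 is wrong in three places.

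**A different group.** A reader might infer that Table 4 describes women other than those randomised. The documents do not support that. The 900 may well contain all 800, and the matching 900 in Table 2 suggests the Masjed-Soleyman cohort used for the city comparison under a wrong header.

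**Intention-to-treat.** A reader might also infer that this population is ambiguous by 100 women and that treatment effects would be diluted. No section plans to analyse the 900 as treated. The text identifies the randomised women as deficient, and women who were never randomised cannot enter a comparison between randomised arms.

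**Selection bias.** The z of 4.9 might be read as proof of biased selection. It is not: the quota gap of about 2.6 ng/ml exceeds the 1.6 ng/ml recovered from the table.

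**The other rows.** Their smallest P is .47 (z = 0.72). Multiplied by 1.91 this is z = 1.38, P about .17, so the overlap hides no significant difference there.

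**The fit.** The 400/400 split is planned, not reported as achieved, and the inference rests on rounded quartiles. This too stands. Allowing unequal strata still leaves the upper quartile near 14.

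**Conclusion.** The point holds in a limited form. The contradiction between 800 and 900 is certain. That the column includes women above 20 ng/ml is probable; the figure of about 100 such women is a conjecture from fitted curves. The mismatch between P=.01 in Table 4 and the statement of no significant difference in The Second Phase is certain. The factor of 1.9 rests on the 900 being a subset of the 1581.

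Together these mean that Table 4 as printed cannot support the conclusion that selection was unbiased. The column may not be the randomised set, the test is not valid for overlapping groups, and comparing mainly deficient women with a sample that includes sufficient women does not show how 800 were chosen from among the deficient. The vitamin D row is uninformative in either direction, because a gap is built in by design. Nothing here shows that selection was biased, or that the eight-arm comparison is compromised.

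**What to change.** 1. State one number of randomised women and use it in the abstract, The Second Phase, Results and Table 4.
2. Say who the 900 are, reconcile them with the 900 in Table 2, and relabel the column. If some are women above 20 ng/ml, they should not appear under a heading of allocated women.
3. Rebuild the check with disjoint groups within each severity class: deficient women randomised against deficient women not randomised.
4. Withdraw or restate the conclusion in The Second Phase, and report the vitamin D difference (P=.01) consistently with the Results text.

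The cost is one re-run descriptive table from data already collected, plus a few corrected sentences. No sample size or planned outcome analysis changes. The statement about selection will probably have to be more cautious.
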